### Intervention: ‘Relearning how to think’ programme

This is a brief online intervention designed to modify negative emotional interpretation biases. The intervention is composed of four different sessions in audiovisual format with psychoeducational content, open-answer questions, and exercises to be completed by users. Different cognitive biases, such as jumping to conclusions, mental filter, overgeneralisation, and negative attributions, are targeted in each session following classical descriptions of biases [7, 41]—see Fig. 1. The organisation of the content of the sessions was based on the Cognitive Error Rating Scales (CERS) [42], a manual created for therapists to evaluate cognitive errors during clinical sessions, and the CBM-errors [43], a clinical strategy to promote more benign interpretations following Beck’s theory [24].

**Fig. 1 Fig1:**
[figure not shown]
Classification of the specific cognitive biases targeted in the four online sessions of the programme

Each session of ‘Relearning how to think’ is composed of four different parts (see Fig. 2). In part 1, participants receive information about specific interpretation biases and are given examples in video format. Some of these videos are daily life scenes where professional actors represent examples of cognitive biases (following clinical vignettes described elsewhere) [6]. During each video (before the resolution of the scene), and to increase active involvement, participants have to complete an open-ended question about what could happen in those ambiguous situations. In the second part, users are informed about the risks of using negative interpretations, which is followed by an explanation of the strategies to avoid them in part 3. These strategies are based on ‘the 4-questions technique’ [44], widely used in clinical practice. This technique involves 4 steps to re-evaluate the negative interpretation of a given situation: 1) finding evidence for the negative interpretations, 2) uncovering the cognitive bias present in the situation, 3) identifying the negative consequences, and 4) creating alternative ways of thinking. Finally, during part 4, participants have the opportunity to practice the strategies in an exercise composed of imagery training [45] followed by negative scenarios in an audio format aimed to be reinterpreted. Figure 3 shows the steps of the exercise. It starts with an imaginary training [45] aimed to make scenarios more vivid to users. Participants are presented with a screen saying ‘Close your eyes. Imagine.’ for 1 s followed by a black screen during which a negative scenario is played in audio format with a female voice (e.g. *Your partner travels to work by car and normally arrives home promptly every day. Today you notice that they are over an hour late. Your first thought is that there must have been a crash*). Audio scenarios are daily life situations where negative interpretations arise, and participants are asked to imagine themselves in those situations. A beep is played for users to open their eyes and start with the exercise questions. First, they have to rate their mood (sadness, happiness, anxiety, and anger) on a 10-point VAS scale based on the most frequent emotions experienced in daily life [46, 47]. Then, they are guided to apply the 4 questions technique to each scenario. Finally, users evaluate the degree to which they believe in the new alternative thoughts and emotions generated by the new scenario (sadness, happiness, anxiety, and anger).

**Fig. 2 Fig2:**
[figure not shown]
Structure of each session of the programme

**Fig. 3 Fig3:**
[figure not shown]
Practice exercise of each session of the programme

### Cognitive bias measures

#### Ambiguous Scenarios Test for Depression-II

The AST-D-II [48] is a self-report measure of interpretation biases. It consists of 15 ambiguous scenarios which participants have to rate on a scale from −5 (very unpleasant) to 5 (very pleasant). Participants are asked to imagine each scenario as vividly as possible and as if it was happening to them (e.g. *As you enter the room, the commission welcomes you and begins with the oral examination. After just a few minutes you know intuitively how the examination will go*). Two parallel versions are used in counterbalanced order at baseline, post-treatment, and follow-ups. Participants’ responses to the items were transformed into a total sum score by adding up the values of each item, rescaled from 1 to 11 (higher scores represent more positive interpretations). Internal consistency is good (*α* = 0.87) for the general scale and also for its two short versions A (*α* = 0.77) and B (*α* = 0.78).

#### Mouse-based (gaze) Contingent Attention Task (MCAT) [49]

A variant of the original Scrambled Sentence Test (SST) [50] is used to measure interpretation bias while monitoring attention towards emotional stimuli, based on the same principles as in the Eye-gaze Contingent Attention Training (ECAT) [51]. At the beginning of the task, participants have to click a fixation cross at the left side of the screen to elicit natural left-to-right reading patterns. Then, the *reading screen* is presented with a six-word emotional scrambled sentence (e.g. ‘am winner born loser a I’) where each word is hidden with a blank mask. Participants are instructed to move the mouse cursor over each mask to read the hidden word and mentally form a grammatically correct sentence using five of them. They are given a time limit of 14 s per sentence. This procedure is used to objectively measure attention biases toward emotional words (negative or positive). Then, the *answer screen* is presented with the six words unmasked for participants to click the order of the sentence they had mentally formed. In this section, participants are given a time limit of 7 s. Two are calculated from this procedure. First, the time spent (in ms) reading negative words divided by the total time spent (ms) reading positive and negative words is the index of overall negative attentional bias. Second, the resulting ratio of correctly unscrambled negative sentences and correctly unscrambled positive and negative sentences is considered to be the index of automatic negative interpretation bias [51]. In both cases, higher scores indicate higher negative cognitive biases. To maximise the appearance of biases, at the beginning of the task, participants are presented a six-digit number for 5 s and told to keep that number in mind during the entire task as they will be asked to retrieve it at the end of the task. This procedure will be completed by participants at both pre- and post-intervention evaluations.

#### Memory bias task

As a measure of memory biases, participants are given 5 min to remember the sentences they constructed during the MCAT procedure. Following Everaert et al.’s procedure [31], the ratio between negative sentences and the total number of emotional sentences recalled will be used as an index of negative memory bias. This procedure will be completed by participants at both pre- and post-intervention evaluations.

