It is hypothesised that there will be a significant change in interpretation bias (less negative or more positive/neutral) from pre-intervention to post-intervention in the experimental group in comparison to the control group. It is also expected that changes in interpretation biases will also be associated with significant changes in attention and memory biases (less negative or more positive/neutral) from pre-intervention to post-intervention in the experimental group in comparison to the control group. Finally, it is hypothesised that the intervention will help the experimental group to reduce symptoms of depression and anxiety and increase well-being from pre-intervention to post-intervention in comparison to the control group. Due to the lack of conclusive findings from previous studies, it is explored whether these changes are maintained over time (after 2 weeks and 3 months) and the temporal dynamics of the different cognitive bias processes (attention, interpretation, and memory).

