### Randomisation and blinding

This study is a randomised superiority trial with two parallel groups and a 1:1 allocation ratio. Participants will be randomly allocated to the experimental group (CBM_Clin_) or a control waiting list group. This control group was chosen due to the novelty of the intervention, for which a waiting list is recommended to get a first impression of its effects [38]. Randomisation will be conducted by the main investigator using an Excel macro. This method assigns a different code to each group, which will only be known by the researchers. In this trial, solely participants will be blinded to their allocation and the meaning of codes.

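### Only participants are blinded, so any hand scoring of the sentence-recall (memory bias) task would fall to people who can know the arm

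*Protocol article*

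**What the plan says.** Randomisation and blinding (protocol article) fixes who knows what. The allocation is made by the main investigator: "Randomisation will be conducted by the main investigator using an Excel macro". On the codes: "This method assigns a different code to each group, which will only be known by the researchers". On blinding: "In this trial, solely participants will be blinded to their allocation and the meaning of codes".

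Memory bias task describes the outcome: "participants are given 5 min to remember the sentences they constructed during the MCAT procedure", after which "the ratio between negative sentences and the total number of emotional sentences recalled will be used as an index of negative memory bias". The section attributes the index to a cited procedure. It does not state who scores, whether responses are typed, written or spoken, or how an incomplete or reworded recollection is handled.

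Objectives and hypotheses gives the outcome a directional between-group role, expecting that "changes in interpretation biases will also be associated with significant changes in attention and memory biases", towards less negative bias in the experimental group than in the control group.

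**The concern.** Most of the other outcomes leave a scorer little to decide. The questionnaires are the participants' own ratings, summed. The MCAT attention index is "the time spent (in ms) reading negative words divided by the total time spent (ms) reading positive and negative words". The MCAT interpretation index comes from a screen of supplied words "for participants to click the order of the sentence they had mentally formed". The beads task counts beads by computer.

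Recall of self-built sentences is different in kind. People produce fragments and paraphrases, and unless matching is automated, someone has to decide which of these count. If that person knows the arm and the expected direction, doubtful recollections could be treated differently in the two arms without intent. Rejecting doubtful negatives, or accepting doubtful positives, more readily in the experimental arm would produce the hypothesised reduction in negative memory bias. The Discussion presents the behavioural measures as a guard against respondent bias, and unmasked scoring would weaken that guard for this one measure.

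**Working it through.** The plan gives no recall count, so it has no figure to reproduce here. The sample-size calculation does not bear on this point.

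**Step 1: is unmasked scoring stated or only not excluded?** Randomisation and blinding uses a word of restriction: participants alone are blinded, and the researchers hold the codes. Procedure adds other routes to the arm. The main investigator creates the sequence, the researchers monitor session completion in the experimental arm, and the feedback question comes at post-assessment for the experimental arm but only at follow-up for controls. Masked scoring would therefore depart from the stated rule. That a person scores recall at all is not stated.

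**Step 2: what can a scorer decide?** Each emotional MCAT item offers opposing target words (the article's example contains both winner and loser), and the participant clicks the sentence formed. The interpretation index needs the valence of each built sentence, so that valence is available. A recollection attributable to an item can be checked against it. The realistic discretion is accept or reject.

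**Step 3: effect of one decision on one participant.** Let n be the clear emotional sentences recalled and p the negative share.
- Accepting a doubtful negative changes the ratio by (1 - p)/(n + 1).
- Accepting a doubtful positive changes it by -p/(n + 1).

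Both n and p are assumed:

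| Clear sentences (negative) | Ratio | Accept one negative | Accept one positive |
|---|---|---|---|
| 5 (2) | 0.400 | 3/6 = 0.500 (+0.10) | 2/6 = 0.333 (-0.07) |
| 8 (3) | 0.375 | 4/9 = 0.444 (+0.07) | 3/9 = 0.333 (-0.04) |
| 12 (5) | 0.417 | 6/13 = 0.462 (+0.045) | 5/13 = 0.385 (-0.03) |

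**Step 4: what systematic leaning would do between arms.** Assumptions: true negative ratio 0.40 in both arms, SD 0.15 to 0.25, 73/2 = 36.5 per arm, and a simple two-arm comparison of post scores at two-sided 5%. If a share s of negative recalls is rejected in the experimental arm only, its ratio becomes 0.40(1 - s)/[0.40(1 - s) + 0.60]. The standard error of d is √(2/36.5) = 0.234.
- s = 0.10: 0.36/0.96 = 0.375, a difference of 0.025. Spurious d is 0.10 (SD 0.25) to 0.17 (SD 0.15), and the false-positive rate is 7% to 11%.
- s = 0.20: 0.32/0.92 = 0.348, a difference of 0.052. Spurious d is 0.21 to 0.35, and the false-positive rate is 14.5% to 32%.

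These rejection rates only illustrate sensitivity. Nothing in the article suggests that they occurred.

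**The case against.** The strongest reply is that the article never says a person scores recall. Responses could be typed and matched by machine. The cited procedure may contain an exact match rule, and an article may properly leave such detail to the full protocol. This stands in part: the missing match rule is not itself a fault, and the need for judgement remains an inference. But a match rule would not mask the scorer, and the blinding sentence is a positive statement rather than a gap.

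A reader might infer that scoring is, as written, done by people who know the arm. The article does not support that. It says who knows the codes and who is blinded, and does not mention outcome scoring.

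A reader might also take one decision to be worth 0.11, the distance between 4/9 and 3/9. That requires the same recollection to be countable as either negative or positive. Since valence can be checked against the clicked sentence, the 0.11 adds two separate shifts (0.07 and 0.04) that apply to different sentences.

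The remaining objections limit the weight of the point. Interpretation bias is the target of the intervention and the basis of the sample size, while memory bias is a further hypothesis. Trial status reports completion by 30 December 2020, so a change helps only if recall is still unscored or can be re-scored.

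**Conclusion.** The point holds as a minor, low-confidence improvement. The stated blinding leaves any manual scoring of recall to people who can know the arm, and recall is the hypothesised between-group outcome most open to scorer discretion. On the assumed 8 clear sentences with 3 negative, one accept-or-reject decision moves a participant's ratio by +0.07 or -0.04. A trial-level bias would need scoring that is manual, unmasked and applied differently by arm. The article shows only that masking is not planned; it does not establish the other two conditions. There is no evidence that memory scores were biased, and the sample size and the interpretation-bias measures are untouched.

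**What to change.** Amend Randomisation and blinding and Memory bias task to say that any recall needing human judgement is scored as follows:
- by an existing team member, against the participant's own MCAT sentences;
- from a shuffled file stripped of group code and session label (pre or post);
- under a match rule fixed beforehand, covering partial and reworded recollections;
- with scores locked before they are linked to arm.

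If matching is fully automated, one sentence saying so is enough. If data collection has ended, apply the same steps to the stored raw recall records where these are kept.

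The cost is a small data-handling step and a short delay before memory scores can be linked. No extra staff, visits or participants are needed.

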**Fig. 4 Fig4:**
[figure not shown]
Schedule of enrolment, interventions, and assessments

After completion of the three lab tasks, participants in the experimental group will receive in their email the link to complete the online programme from home. They will need to log in to an online platform created for this study and will be invited to create their own account and password to access the materials. Information will be stored solely using the participant’s code number and only the main researchers will have access to the data. These data will be recorded in the database of the platform and will be used by the researchers to monitor if participants in the experimental group complete all four online sessions before the post-intervention evaluation. When participants first access the platform, they will find only the first session available. Access to the next session will be granted only 24 h after completing the previous one. This intermission between sessions aims to enhance participants’ processing of the contents of each session as well as to avoid cognitive overload and boredom.

After finishing the 4-session training programme, participants in the experimental group will be notified again, after approximately 10 days, for a second assessment session. The control group will be allowed to complete the intervention right after the second assessment. To improve adherence, both groups will receive a reminder for the second assessment session the day before. Finally, participants will be sent the follow-up questionnaires (AST-D-II, DASS-21, PHI, SE) twice (in the next 2 weeks and 3 months). To increase adherence during the follow-ups, participants will be sent up to a maximum of three reminders to complete questionnaires. Both groups will have the opportunity to complete a ‘feedback question’ to give their opinion about the intervention. This question will be included in the post-assessment for the experimental group and at the follow-ups for the control group.

The procedure has been approved by the university ethics committee (Ref. 2018/19-017) and has been registered (ClinicalTrials.gov NCT03987477). Moreover, it follows the recommendations for a clinical trial protocol [70].

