### Analytic plan

Demographic data and pre-treatment measures will be analysed to test for group differences with analysis of variance and chi-squared test for nominal variables.

Complete case analyses will be conducted for those participants who complete all 4 online sessions and attend pre- and post-assessment evaluation sessions. A series of 2 (group: experimental, control) × 3 (symptom group: never, present, past) × 2 (time: pre-training, post-training) analyses of variance will be performed to evaluate the change between groups. The symptom group will be created based on present and past symptoms of depression and/or anxiety to explore their influence on the results. Intention-to-treat (ITT) analyses will be conducted with all participants, regardless of session or outcome measure completion. ITT mixed models (restricted maximum likelihood (REML) estimation) will be used to account for missing data [71]. Binary logistic regression will be used to evaluate the assumption that data is Missing at Random (MAR). Exploratory mediation analyses will be conducted to study the interplay between the different cognitive bias scores given the change of the intervention. Finally, follow-up assessments will be included in a series of analyses of variance to evaluate group differences in time. All analyses will be performed in SPSS Statistics 20 with an *α* level of 0.05.

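### The memory-bias index is scored on the participant's own MCAT sentences, so it follows the MCAT interpretation index even when memory has no bias

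*Protocol article*

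**What the plan says.** Under the MCAT heading, the protocol article defines automatic negative interpretation bias from the sentences the participant forms: "the resulting ratio of correctly unscrambled negative sentences and correctly unscrambled positive and negative sentences is considered to be the index".

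Under Memory bias task, the same sentences become the material for recall: "participants are given 5 min to remember the sentences they constructed during the MCAT procedure". The score is then fixed: "the ratio between negative sentences and the total number of emotional sentences recalled will be used as an index of negative memory bias". Nothing in the article divides by, subtracts or conditions on the share of negative sentences that were built.

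Both scores feed a stated hypothesis and a planned analysis. Objectives and hypotheses says: "It is also expected that changes in interpretation biases will also be associated with significant changes in attention and memory biases", comparing the experimental group with control from pre to post. The Analytic plan adds: "Exploratory mediation analyses will be conducted to study the interplay between the different cognitive bias scores given the change of the intervention". The Discussion presents the link between interpretation, attention and memory as a distinctive contribution of the trial.

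**The concern.** The two indices are meant to describe different processes, but the second is computed on a subset of the items that make up the first. A participant who builds fewer negative sentences after the programme has fewer negative sentences available to recall. The recalled negative share is then expected to fall even if memory works exactly as before.

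At stake is the interpretation of any link between interpretation and memory. As scored, the data cannot separate transfer to memory from a change in which sentences were built. The trial could report such transfer when recall had no valence preference at all.

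**Working it through.** **The plan's own figure.** The Sample size section gives *d* = 0.43, alpha 0.05, power 0.95, N = 73, and 88 after adding 20%. Take f = 0.43/2 = 0.215 and a pre-post correlation of 0.5 (assumed; the article gives none). The noncentrality for the group x time test is f²·N·m/(1-ρ) = 0.215² x 73 x 2/0.5 = 13.5. Power is 0.952 at N = 73 and 0.949 at N = 72, so 73 is reproduced, and 73 x 1.2 = 87.6, rounded up to 88. That figure is not in dispute. N = 88 is used below.

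**Algebra.** Let a participant build n₋ negative and n₊ positive sentences.
- Interpretation index: I = n₋/(n₋ + n₊).
- Memory index: M = r₋/(r₋ + r₊), where r₋ and r₊ are the numbers recalled.
- If recall ignores valence, the recalled sentences are a random sample of the built ones. Then E(M | sentences built, at least one recalled) = I, whatever the recall rate.

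**Numerical example** (assumed: 20 emotional sentences, 40% recalled):
- Share built 0.40: 8 negative and 12 positive built; 3.2 and 4.8 recalled on average; 3.2/8.0 = 0.40.
- Share built 0.30: 6 and 14 built; 2.4 and 5.6 recalled; 2.4/8.0 = 0.30.
- The recall rate is 40% for both valences on both occasions, yet the memory index falls by 0.10.

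**Single-occasion correlation with no memory bias** (assumed mean negative share 0.40, SD 0.15): 0.80 with 20 sentences and 40% recall, 0.63 with 10 and 30%, 0.92 with 30 and 60%.

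**Change scores**, which are what the hypothesis concerns. Simulation of trials with N = 88, 800 runs per cell, valence-blind recall. The article gives no sentence counts or recall rates, so these inputs are assumed: 10, 20 or 40 sentences; recall probability 0.2, 0.3 or 0.5; logit-normal negative tendency (mean -0.8, SD 0.8, pre-post correlation 0.6); programme effect on sentence building of 0, 0.43 or 0.8 SD. Mediation is joint significance of group on interpretation change, and of interpretation change on memory change given group. Three of the nine count combinations:

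| Sentences | Recall | Effect (SD) | Change correlation | Association significant | Group x time, memory | Group x time, interpretation | Mediation |
|---|---|---|---|---|---|---|---|
| 10 | 0.2 | 0 | 0.49 | 99% | 5% | 4% | 4% |
| 10 | 0.2 | 0.43 | 0.49 | 99% | 9% | 19% | 19% |
| 10 | 0.2 | 0.8 | 0.50 | 99% | 17% | 50% | 50% |
| 20 | 0.3 | 0 | 0.64 | 100% | 5% | 5% | 5% |
| 20 | 0.3 | 0.43 | 0.64 | 100% | 17% | 32% | 32% |
| 20 | 0.3 | 0.8 | 0.66 | 100% | 41% | 79% | 79% |
| 40 | 0.5 | 0 | 0.86 | 100% | 6% | 7% | 7% |
| 40 | 0.5 | 0.43 | 0.87 | 100% | 36% | 43% | 43% |
| 40 | 0.5 | 0.8 | 0.87 | 100% | 74% | 86% | 86% |

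Over all cells:
- The change correlation is 0.49-0.87, the slope of memory change on interpretation change is 0.99-1.01, and the association is significant in 99-100% of runs.
- Spurious group x time effects on memory occur in 9-36% of runs at 0.43 SD and 17-74% at 0.8 SD. A separate simulation gave about 10-30% and 21-77%.
- Spurious mediation occurs in 19-46% and 50-89%. In each cell this matches the chance of detecting the interpretation effect, because the interpretation-memory path is almost always significant.

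The 0.43 SD here is a shift on the simulated latent scale, not the plan's f, so the detection rates do not re-check the sample size.

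**Conditional indices under the same null.** Recalled share minus built share correlates -0.01 to 0.01 with interpretation change (significant in 4-6% of runs), and its group x time effect is significant in 3-7%. A log odds ratio of recall with a 0.5 correction does less well when few sentences are recalled. Its correlation with interpretation is -0.13 to -0.19 (-0.15 at 10 sentences and 30% recall, where its mean moves from 0.09 to 0.20 as the built share falls from 0.40 to 0.30). At 20 sentences and 40% recall the correlation is negligible (-0.02).

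**The case against.** **The index follows a cited procedure.** True, but a citation does not remove the dependence between two scores taken from the same items.

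**The mediation is only exploratory, and the article does not say which interpretation score enters it.** Both points stand. The AST-D-II also measures interpretation and shares no items with the recall task, so the item overlap concerns the MCAT index. Using the AST-D-II instead would not make the recall ratio a pure memory measure, because it would still follow any real change in which sentences were built. The interpretation-memory association is also a stated hypothesis, not only an exploratory analysis.

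**All counts are assumed.** This stands for the size of the effect. The equality of expected values does not depend on the counts, and the association was nearly always significant across the whole range tried.

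**A stronger reading.** A reader might infer that the whole second hypothesis and the mediation are bound to come out positive. The documents do not support that:
- Only the association between MCAT interpretation change and memory change is near-automatic.
- The hypothesis is framed as experimental versus control. A spurious group effect on memory, or spurious mediation, needs the programme to change sentence building first. Without that both stay near 5%, and at 0.43 SD most simulated trials show neither.
- The hypothesis also covers attention. That index is a ratio of reading times, and the shared-sentence argument does not reach it.
- A lower memory score after building fewer negative sentences is what is expected on average. It need not occur in every participant.

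**Conclusion.** The concern holds for the memory index as defined. With valence-blind recall its expected value is the MCAT interpretation index, so an association between their changes is not evidence of a memory effect. Under the assumed counts that association has a correlation of about 0.5-0.9 and is significant in 99-100% of trials of 88, with or without a programme effect.

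The further consequences are conditional on the programme shifting sentence building, which is what the trial expects. Given such a shift, a spurious group x time effect on memory appears in about 9-36% of trials at 0.43 SD and 17-77% at 0.8 SD, and spurious mediation in about 19-46% and 50-89%.

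The interpretation, attention, symptom and well-being comparisons and the sample-size figure are unaffected. The article fixes this index explicitly, so this is a scoring choice to change and not a detail left to an analysis plan.

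**What to change.** For the interpretation-memory hypothesis and the mediation, replace the recall ratio with a measure conditional on what was built. Two options:
1. Recalled negative share minus built negative share, computed per participant and occasion.
2. A logistic mixed model of recall (yes/no) for each built sentence, with valence x group x time. The three-way term is the programme effect on memory bias.

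Option 1 is simpler and is uncoupled from interpretation when recall ignores valence, which is the null at issue. If recall favours one valence by a fixed amount, the difference still varies somewhat with the share built, so option 2 is the cleaner analysis where the data allow it. The 0.5-corrected log odds ratio should not be the main index, because it stays coupled to interpretation at low recall counts.

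Keep the planned ratio as a descriptive result. The Trial status section reports completion by December 30, 2020, so the replacement should be declared as a change to the published plan.

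Cost: re-scoring of tasks already run, with no new participants or assessments. The conditional index is noisier for people who build or recall few negative sentences. Option 2 also needs recall records linked to the individual built sentences, and the article does not say whether they were stored that way.
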